## Abstract

**Background:**

Tobacco use is responsible for the death of about 1 in 10 individuals worldwide. Mindfulness training has shown preliminary efficacy as a behavioral treatment for smoking cessation. Recent advances in mobile health suggest advantages to smartphone-based smoking cessation treatment including smartphone-based mindfulness training. This study evaluates the efficacy of a smartphone app-based mindfulness training program for improving smoking cessation rates at 6-months follow-up.

**Methods/Design:**

A two-group parallel-randomized clinical trial with allocation concealment will be conducted. Group assignment will be concealed from study researchers through to follow-up. The study will be conducted by smartphone and online. Daily smokers who are interested in quitting smoking and own a smartphone (*n* = 140) will be recruited through study advertisements posted online. After completion of a baseline survey, participants will be allocated randomly to the control or intervention group. Participants in both groups will receive a 22-day smartphone-based treatment program for smoking. Participants in the intervention group will receive mobile mindfulness training plus experience sampling. Participants in the control group will receive experience sampling-only. The primary outcome measure will be one-week point prevalence abstinence from smoking (at 6-months follow-up) assessed using carbon monoxide breath monitoring, which will be validated through smartphone-based video chat.

**Discussion:**

This is the first intervention study to evaluate smartphone-based delivery of mindfulness training for smoking cessation. Such an intervention may provide treatment in-hand, in real-world contexts, to help individuals quit smoking.

**Trial registration:**

Clinicaltrials.gov NCT02134509. Registered 7 May 2014.

## Background

Tobacco use is the leading cause of preventable death worldwide [1]. Although over 70% of smokers want to quit, fewer than 5% achieve this annually [2]. Behavioral treatments teach individuals strategies to avoid smoking triggers, or to foster positive affective states, reduce negative mood, reduce stress by exercise or relaxation, divert attention from cravings, substitute other activities for smoking, or to develop social support mechanisms [3,4]. These approaches have only modest success, with 6–12 month abstinence rates of 20-30% [5,6]. Their limited success may be due to the fact that smoking triggers are always present, making avoidance difficult; diversion of attention requires cognitive resources which are often depleted after strong affective states [7]; and effective substitutions are not always readily available.

Recent work suggests that mindfulness training may be an effective behavioral treatment for smoking by targeting stress, craving and learned responses. Mindfulness training has been adapted as a central component of some contemporary psychotherapy and has shown some efficacy in the treatment of psychiatric disorders relating to or involving pain, anxiety, and depression [8,9]. Mindfulness has been operationalized into two components: (i) maintaining attention on immediate experience and (ii) maintaining an attitude of acceptance toward that experience [10]. Mindfulness training typically involves the training of attention regulation, body awareness, and emotion regulation, among other components [11]. In this way, mindfulness training may aid in smoking cessation by teaching individuals to pay attention to and work mindfully with affective states and craving as they arise, rather than to react by smoking.

Preliminary evidence supports testing mindfulness training in the treatment of substance-use disorders and other addictions [9,12]. A recent review found that mindfulness-based interventions were associated with reduced consumption of substances of misuse including alcohol, cocaine, amphetamines, marijuana, cigarettes, and opiates, as compared to several active and inactive control groups [13]. Moreover, several studies included in the review [13] report that mindfulness training was associated with reduced craving and increased mindfulness, suggesting a potential mechanism contributing to outcomes. Although several limitations of prior studies were identified such as small sample sizes and lack of methodological details, findings overall suggest that mindfulness training may be an effective treatment for addictions. A recent randomized controlled trial (RCT) reported preliminary evidence that mindfulness training was associated with increased smoking cessation rates as compared to another leading, widely disseminated and validated smoking cessation treatment [14]. In that trial, home mindfulness practice was also found to reduce the association between craving and smoking [15].

Despite these promising findings, in-person mindfulness training is challenged by the need for experienced therapists, significant demands on time, limited access to and high costs of in-person treatment delivery, and other limitations. One way to overcome these challenges is to offer mobile mindfulness training delivered by smartphone. The global use of smartphones is growing, for example nearly half of U.S. adults (age 18+, 45%) and two-thirds of young adults (age 18–29, 66%) now use smartphones [16] (young adults also have the highest smoking rates in the U.S. (32-35%) [17]). Smartphone app-based treatments for addictions are also gaining popularity due to relative low cost, ease of use, and availability [18,19]. This suggests the demand for and utility of a mindfulness training smartphone app for smoking cessation. In addition to improving treatment dissemination, this approach can be standardized compared to in-person training; may reduce stigma associated with seeking treatment for substance use; improves tracking of adherence such as to home meditation practice, as compared to self-report; offers direct access to tools for self-management and social support; and gets treatment into the hand of the individual in context [18]. Beginning work has evaluated the efficacy of smartphone-based treatments for smoking. A recent pilot trial compared SmartQuit, an app teaching acceptance and commitment therapy, which uses mindfulness strategies, to the National Cancer Institute's QuitGuide app for smoking cessation, and found higher engagement and promising quit rates for SmartQuit [20]. Therefore in this study we translate a mindfulness training program that has shown preliminary efficacy for smoking cessation into a smartphone app.

The smartphone app is also embedded with experience sampling [21] to query individuals about their behavior and experience in real time to measure psychological mechanisms of change *in vivo*. By sampling behavior and experience in real time, it is possible to minimize recall bias, maximize ecological validity, and document change over time [21]. Tracking cigarette use in real time also avoids known biases in retrospective reports [22]. Experience sampling has been used successfully across disciplines including mindfulness [23] and smoking cessation [24], and will be utilized here to evaluate smoking, craving, mood, and mindfulness.

This trial is innovative by: (i) mobile mindfulness training merges a new treatment for smoking –mindfulness training –with a novel delivery method –smartphone app; (ii) mobile mindfulness training can potentially improve efficacy by bringing mindfulness into real-world contexts; (iii) experience sampling will capture real time, real-world smoking, craving, mood, and mindfulness, by smartphone app, whereas prior studies were limited to text messaging or web-based tools [23-26]; and (iv) a novel comparison group, experience sampling-only, will be used to disentangle the efficacy of mindfulness training from that of effective self-monitoring.

The primary aim is to evaluate the efficacy of mobile mindfulness training plus experience sampling to improve smoking cessation rates at 6-months follow-up as compared to experience sampling-only. It is hypothesized that mobile mindfulness training will contribute to a significantly higher smoking cessation rate at 6-months follow-up as compared to control. The secondary aim is to test the hypothesis that mobile mindfulness training moderates the decoupling of craving and smoking. It is hypothesized that mobile mindfulness training will moderate the change in the prediction of smoking by craving across study time points. It is also hypothesized that meditation practice during treatment will moderate this change.

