20	Provides tips on staying motivated and maintaining mindfulness practice, subjects write down a mantra to use and set mantra reminder.
21	Quit day ceremony, subjects tell a friend or family member that today is their quit day.
22	Incorporates mindfulness practices as a new, healthy habit, and instructs the user on which modules to return to if they relapse.
Bonus	“Big Mind Meditation” audio by Joseph Goldstein; Tree Analogy for reinforcing noting video; Attitude is Everything video; “Mountain Meditation” audio by Joseph Goldstein; Sitting Meditation audio

Participants will also be taught an informal mindfulness practice to work mindfully with cravings: Recognize, Accept, Investigate, and Note (“RAIN”) what cravings feel like as they arise and pass away. RAIN is accessible from the home page of the app so that participants may use it any time they have a craving to smoke by choosing the “Want-O-Meter.” They are directed to identify their smoking trigger, rate their craving, and choose between using RAIN to ride out their craving, or completing an audio-guided exercise to ‘smoke mindfully’ by paying attention to the moment-to-moment experience and bodily sensations of smoking.

Social support has been shown to boost quit rates [32], therefore the app is also paired with a closed online community, built on the Ning platform (www.ning.com). Features include: (1) video tutorials of how to use the app; (2) quit buddy sign ups, for individuals to go through the process with a peer; (3) forums for posting questions and insights; (4) a “Tip of the week;” and (5) an “Ask the Doc” feature to get answers from an “expert” (JB). Participants can access the community beyond their quit date in order to encourage others to quit and to bolster their own abstinence.

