Additional app features include: (i) “Activity Feed” tracks interaction with the app and can be shared on the community; (ii) “My Morning Stats” tracks daily smoking to encourage a gradual taper, and daily and monthly financial savings; (iii) “Night Reflection” to reflect on daily smoking, with links to journal on the community and practice an audio-guided body scan or loving kindness meditation; (iv) “Reminders Settings” to adjust times/days to receive reminders including “Morning Stats Motivator,” “Goal Reminder,” “Check-ins,” and “Night Reflection;” (v) “My Quit Pact” which can be personalized across the intervention and includes quit date, money saved, reasons for quitting, triggers to watch for, and a personalized mantra; and (vi) “Tracker,” to track cigarettes smoked.

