## Discussion

This trial is the first to test smartphone app-based mindfulness training to for smoking cessation. Although many meditation-related smartphone apps are available, very few have been tested for use in clinical groups such as smokers [18]. In addition, there are currently few smoking cessation interventions that target the association between craving and smoking [12]. In-person mindfulness training has been found to improve smoking cessation rates and decrease the association between craving and smoking [14]. Therefore, this trial will test whether mobile mindfulness training is associated with similar outcomes.

The choice of a control group for this trial was critical for isolating and testing variables of interest, by comparing mobile mindfulness training to experience sampling-only. Alternative comparators could be in-person mindfulness training, an online smoking cessation program, waitlist control, or another smartphone-based smoking cessation intervention. However, there is limited evidence for the efficacy of existing smartphone apps for smoking cessation, and other apps offer additional features not available in the tested intervention that introduce confounds, or vice versa. Experience sampling may bring awareness to smoking, craving, and mood, similar to mindfulness training, therefore experience sampling-only was chosen as the control, to disentangle the effects of mindfulness training from those of effective self-monitoring. Exploratory analyses will test whether experience sampling-only also leads to mindfulness, and whether increases in mindfulness are associated with smoking cessation.

If the intervention is found to be effective, this RCT will provide a platform for large-scale clinical trials to compare mobile mindfulness training to active behavioral treatments for smoking cessation, and to disseminate this treatment to the wider community.

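### The control is said to isolate mindfulness training from self-monitoring, but the contrast as described estimates the effect of a whole program that also includes an online community and a taper and savings display

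*Protocol article*

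**What the plan says.** All references are to the Protocol article.

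**The claim.** The Background, in its list of innovations, says "a novel comparison group, experience sampling-only, will be used to disentangle the efficacy of mindfulness training from that of effective self-monitoring". The Discussion states "The choice of a control group for this trial was critical for isolating and testing variables of interest" and later "therefore experience sampling-only was chosen as the control, to disentangle the effects of mindfulness training from those of effective self-monitoring". The primary aim in the Background sets mobile mindfulness training plus experience sampling against experience sampling alone, and the hypothesis credits mobile mindfulness training with a higher cessation rate at 6 months.

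**The intervention.** The Intervention group subsection defines mobile mindfulness training as 22 modules. After Table 1 it adds a community: "Social support has been shown to boost quit rates [32], therefore the app is also paired with a closed online community". This includes forums, a weekly tip, a feature for putting questions to an expert, and "quit buddy sign ups, for individuals to go through the process with a peer". Among the additional app features is a morning display that "tracks daily smoking to encourage a gradual taper, and daily and monthly financial savings".

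**The control.** The Control group subsection describes experience sampling only. It names three things controlled for: expectancy, non-specific effects of using a smartphone, and effects of experience sampling. During treatment it matches the sampling procedures; from day 22 it matches all study procedures.

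**The view of unmatched features.** The Discussion argues against other smartphone apps as comparators partly because "other apps offer additional features not available in the tested intervention that introduce confounds, or vice versa".

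**The concern.** A two-arm trial attributes a difference to one ingredient only if that ingredient is all that differs between the arms. Here the intervention group appears to differ from control in at least three ways: the mindfulness modules, the community, and the taper and savings display. The protocol expects the second of these to affect the primary outcome, since that is its reason for including it. It also treats unmatched features as confounding when it considers other comparators.

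What is at stake is the meaning of a positive primary result. Readers told that the control isolates mindfulness training will take a difference in abstinence as evidence for mindfulness. The same result could arise in part from peer support, expert contact or smoking and savings feedback. A larger sample would not help, because the problem is one of attribution and not of precision.

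**Working it through.** No figure in the plan is in dispute, so the check sets the descriptions of the two arms side by side.

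| Component | Intervention group | Control group |
|---|---|---|
| Experience sampling check-ins | Yes | Yes, stated as matched |
| Cigarette Tracker | Yes | Probably: check-in item 8 refers to it, and Secondary outcomes uses it to measure smoking |
| Entry of cigarettes per day, quit date, tutorial | Yes | Yes, stated |
| 22 mindfulness modules and RAIN | Yes | No |
| Online community with buddies, forums, tip and expert questions | Yes | Not mentioned |
| Morning display of taper and savings | Yes | Not mentioned |
| Follow-up emails, surveys, carbon monoxide check | Yes | Yes, from the day-22 matching sentence |

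**Step 1: are the two features absent from the control?** The article does not itemise the control app, so this is inferred from three things: the experience sampling-only label, a matching sentence that covers only sampling procedures during treatment, and the placement of both features under the intervention group. The list of things controlled for omits social support. A control app with the community and the display would hardly fit its label.

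**Step 2: does the day-22 sentence restore balance?** Read naturally, it refers to emails, surveys and carbon monoxide checks. Even a wider reading would leave the 22 days of treatment unmatched.

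**Step 3: what does the contrast estimate?** Write the difference in abstinence as D = m + s, where m is the part due to the mindfulness modules and s the part due to the community and display, including any interaction with the modules. The trial observes D only. For the planned 20-point difference (Sample size), m = 20 and s = 0 gives D = 20 + 0 = 20, and m = 10 and s = 10 gives D = 10 + 10 = 20. These splits are arbitrary and serve only to show that the data would look the same. The protocol gives no information on s.

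**Step 4: do the planned analyses separate m from s?** The regression under Secondary outcomes uses group, craving, and formal and informal practice. It names no term for community use. The Exploratory outcomes plan mediation analyses, but the listed measures include none of social support. Neither analysis recovers the community's contribution.

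**The case against.** The strongest reply is that this is a pragmatic trial of an app-based program and the primary aim already names a treatment contrast. The Discussion draws its consequences from the intervention being effective, and the stated separation is from self-monitoring, not from every other component. Much of this stands. Randomization supports the contrast, and self-monitoring through check-ins is matched. What does not stand is the step from there to mindfulness training. The protocol defines that training as the modules, so an aim and hypothesis phrased in its name do not plainly cover the community.

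It can also be said that the full protocol may itemise the control app. That is fair, and it is why the imbalance is stated as an inference. The point nevertheless concerns a claim the article makes, not a detail it leaves out.

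The planned practice and mediation analyses do bear on mechanism, as does the exploratory check of whether experience sampling alone raises mindfulness. They are relevant, but they do not identify the component effect.

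A reader might be tempted to go further in three directions that the document does not support:

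- **Community access up to the 6-month endpoint.** The text says only that access extends past the quit date and gives no end.
- **Mantra, quit pact and reminders as further non-mindfulness extras.** The mantra belongs to module 20. The pact's reasons, triggers and quit date correspond to modules 2, 6 and 21. The reminders include those for check-ins, which are probably shared.
- **A numerical share of the effect due to social support.** No such figure is given, and any value would be pure assumption.

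**Conclusion.** The point holds as one about attribution. The randomized contrast is a valid estimate of the effect of the whole Craving to Quit program (modules, community and app tools) plus experience sampling, compared with experience sampling alone. It does not support the statements that the control isolates mindfulness training or separates it from self-monitoring, because at least the community and the taper and savings display appear to come with the modules.

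This rests on one assumption: that the control app lacks those two features, as its label and the matching sentence indicate. If the full protocol shows that both are shared, the point falls away for them. No size can be given for the part of any difference due to them. A reader might infer that the primary comparison is invalid or biased; it is not. The primary outcome, test and sample size are unaffected.

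**What to change.** State the primary aim, hypothesis and planned conclusion as the effect of the whole program, with modules, community and app tools named, plus experience sampling versus experience sampling alone. Remove or qualify the statements in the Background and Discussion that the control disentangles or isolates mindfulness training. One sentence acknowledging that social support and the taper and savings display are not described as matched would be enough.

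The cost is wording and a narrower headline claim. Giving the control app the same non-mindfulness features is a separate design trade-off. It would change the comparator, and the point does not require it.

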## Methods/Design

A pragmatic RCT funded by the American Heart Association will be conducted. Participants will be allocated to either the control (experience sampling-only) or intervention (mobile mindfulness training plus experience sampling) group by basic randomization, using Yale Qualtrics Survey Tool (http://www.qualtrics.com/). Ethical approval for the procedures of this trial was obtained from the Yale University Institutional Review Board Human Investigation Committee (HIC #1301011337).

### Setting

The study will be conducted online and by smartphone. Treatment delivery will be smartphone-based. Participants (*n* = 140) will be recruited using online advertising (e.g., http://www.google.com/ads/) and directed to the study website. This recruitment method has been used to register 89 participants and randomize 16 participants per week [27]. This approach will have broad reach.

### Participants

Participants will be eligible if they are: age 18–65 years; smoke at least 5 cigarettes per day; less than 3 months abstinence in the past year; own an iPhone (https://www.apple.com/iphone/) or Android (https://www.android.com/intl/en_us/); and are motivated to quit, as indicated by a score of at least 9 of 10 on the Contemplation Ladder [28], and at least 4 of 5 on one item of the Action subscale of the Readiness to Change Questionnaire [29]. “I am trying to smoke less than I used to” from 1=Strongly disagree to 5=Strongly agree” ”. If smartphone ownership is found to be a barrier to recruitment, smartphones and/or voice/data plans will be provided.

### Recruitment and randomization

All study procedures will be automated using Yale Qualtrics Survey Tool. The study website links to a short screening survey. The survey notifies an individual if they are eligible or not eligible. If eligible, they are asked for their contact information and directed to an online consent form, which includes study contact information to ask questions. Those who provide consent are sent an email with a link to the baseline survey and a copy of the consent form. This email also includes a recommendation for nicotine replacement therapy or other pharmacotherapies [19]. At the end of the baseline survey, participants are randomized to treatment group and emailed a link to download their app and begin the study.

